### Exclusion criteria

The exclusion criteria include the following: (1) Severe comorbidities that prevents patients from cooperating with treatment, such as severe heart disease, severe bleeding, coagulation disorders, etc.; (2) Severe spasticity of the affected upper limb; (3) Skin damage of the affected upper limb; (4) History of mental illness; (5) Pregnant and lactating women.

### Study setting

The treatments will be carried out in Yueyang Hospital of Integrated Traditional Chinese Medicine and Western Medicine. Patients participating in the study are required to sign an informed consent form and voluntarily participate in the study. Primary outcome is FMA-UE, secondary outcomes are the Montreal Cognitive Assessment (MoCA), activities of daily living (ADL), quality of life (QOL), the pain visual analogue scale (VAS-pain) and fMRI. The trial (SPIRIT) schedule for patient enrolment, interventions, and assessments is shown in Fig. 2.

**Fig. 2 Fig2:**
[figure not shown]
The SPIRIT schedule of enrolment, interventions, and assessments

### Sample size

The sample size was calculated based on the main efficacy indicator (FMA-UE score). We referred to a previous similar study as the basis for estimating the sample size [23]. The means and standard deviations (SDs) of FMA-UE scores in the two groups were 30.41 ± 9.07, 23.00 ± 5.58. The sample size estimation formula is as follows:$$ n=\frac{{\left({Z}_{\upalpha}+{Z}_{\beta}\right)}^2{\sigma}^2}{{\left({u}_r-{u}_c-\varDelta \right)}^2} $$

In this formula, *n* is the required number of each group; Assuming one-sided *α* = 0.025 and one-sided *β* = 0.1; The value of Δ is 10% of the mean of the control group in the previous similar study [24]; The required sample size is 13 in each group; Considering a 20% dropout rate, a total of 32 participants should be recruited (16 per group).

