### Randomization and allocation

Randomization is conducted by an independent investigator who is not involved in the recruitment, assessment, treatment, or data analysis. The randomization sequence is generated by computer-generated random numbers. Thirty-two eligible patients are randomly divided into VRMT group and RAVRMT group in a ratio of 1:1. The assignment of patients is concealed in an opaque, sealed envelope, and cases are numbered by an independent investigator in the order of entry into the group. Before starting an intervention, inform therapists of the patient’s specific number and intervention information in order to obtain the assigned treatment.

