### Statistical analysis

Blind the statistician. The clinical data will be analyzed by SPSS25.0 software. For the measurement data of the obtained data, the normality test is first performed. For the measurement data conforming to the normal distribution, it is expressed as the mean ± standard deviation (x ± s). The paired t test is performed before and after the two groups, and the comparison between the two groups is used Two-way repeated measures analysis of variance (2-way repeated measures ANOVA) test. The non-normally distributed measurement data before and after a group of self-comparison uses the Wilcoxon signed rank test, and comparison between the two groups uses the Mann-Whitney signed rank test. The significance level of the statistical test is set to α = 0.05, and the one-sided test is performed. A data monitoring committee will not be implemented because all participants will be treated and adverse events are expected to be low.

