## Discussion

Mirror therapy is based on the theory of mirror neuron system (MNS) and has been widely used in post-stroke rehabilitation [34]. The MNS refers to the brain regions that activate when an individual performs a specific action and when others are observed performing the same or similar action [35]. The human MNS includes the bilateral posterior inferior frontal gyrus (Broca’s area on the left), the ventral premotor cortex, the inferior parietal lobule (angular/supramarginal gyrus), the posterior superior temporal gyrus (Wernicke’s area on the left) [34]. The bilateral posterior inferior frontal gyrus, the ventral premotor cortex, the inferior parietal lobule are all brain regions involved in motor execution [36]. Mirror therapy can improve upper limb motor dysfunction in stroke patients by activating MNS [12, 13]. Virtual reality is used to improve the “immersion” of patients in the process of mirror therapy and reduce the influence of external interference factors [14].

Robot-assisted therapy (RAT) can provide programmed upper limb task training to simulate normal upper limb functional movements. Robot-assisted programmed task training activates cortical striatum pathways that promote motor control, action selection, and reward [37]. The reward generated by RAT guides motor learning through dopamine secretion [38]. In the treatment of upper limb motor dysfunction in stroke patients, RAT can restore upper limb function by activating motion-related brain networks and reward circuits [17].

RAT and VRMT are both promising treatments for improving upper limb motor dysfunction in stroke patients [39]. Combined application of RAT and VRMT could theoretically activate MNS and reward circuits to a greater extent, but further high-quality research is needed before the RAVRMT robot can be widely used in clinical practice. Therefore, we design a single-center, assessor-blinded, randomized controlled clinical trial to observe if the RAVRMT robot can better improve upper limb motor dysfunction after stroke.

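### The sample size is built on a margin Δ that no named test uses, so the planned 90% power is not the power of the comparison that will be run

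*Protocol article*

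**What the plan says.** **Sample size section.** The printed formula has the squared term (u_r − u_c − Δ) in the denominator and σ² without a factor 2 in the numerator. The inputs are:

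- error rates: "Assuming one-sided *α* = 0.025 and one-sided *β* = 0.1";
- earlier data: "The means and standard deviations (SDs) of FMA-UE scores in the two groups were 30.41 ± 9.07, 23.00 ± 5.58";
- the margin: "The value of Δ is 10% of the mean of the control group in the previous similar study";
- the result: "The required sample size is 13 in each group", then "Considering a 20% dropout rate, a total of 32 participants should be recruited (16 per group").

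The section does not say which of the two means is the control. It cites one earlier study for the means and a different reference for Δ. It does not say whether Δ is a superiority or a non-inferiority margin.

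**Statistical analysis section.** For normally distributed data, "the comparison between the two groups is used Two-way repeated measures analysis of variance (2-way repeated measures ANOVA) test". For non-normal data a Mann-Whitney test is named. The level is 0.05, one-sided. No margin, shifted null or confidence-limit rule appears there or elsewhere.

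**Aim.** The Discussion describes the trial as designed "to observe if the RAVRMT robot can better improve upper limb motor dysfunction after stroke". The Abstract words it in the same way, without a margin.

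**The concern.** A formula with Δ subtracted from the expected difference sizes a test whose null is a difference of Δ. The two between-group tests that are named have a null of no difference. The test and the stated aim agree with each other; the sizing is the part that is out of line.

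At stake is what the 90% means. A reader will take it as the chance that the planned comparison of FMA-UE is significant if the assumed effect is real. It is not that. If the result is negative, the reader will also overrate how firmly a benefit of the assumed size has been excluded. The two sections also use different one-sided levels (0.025 and 0.05), so any restated power has to say which level it refers to.

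**Working it through.** **Inputs (Sample size section).** Difference 30.41 − 23.00 = 7.41. Control mean taken as 23.00, because u_r − u_c should be positive; then Δ = 0.10 × 23.00 = 2.30. If 30.41 were the control mean, Δ would be 3.04. Multiplier (1.960 + 1.282)² = 10.507. Root-mean-square SD = √[(9.07² + 5.58²)/2] = √56.70 = 7.53.

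**Step 1: the plan's own figure.** The printed formula with the smaller SD gives

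n = 10.507 × 5.58² / (7.41 − 2.30)² = 10.507 × 31.14 / 26.11 = 12.53, rounded up to 13.

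This matches, but it does not identify the hypothesis that was intended, because other routes also reach 13:

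- the usual factor 2, SD 7.53 and the opposite sign for Δ: 2 × 10.507 × 56.70 / 9.71² = 12.64;
- Δ = 0, a t-based calculation with SD 5.58 at one-sided 0.025: power 90.1% with 13 per group (87.5% with 12);
- Δ = 0, the printed formula with SD 9.07 at one-sided 0.05: 12.83.

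For the total, 13 × 1.2 = 15.6, rounded up to 16 per group.

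**Step 2: power of a zero-difference test.** A two-sample t test stands in for the between-group comparison. Power is the probability that a noncentral t variable with 2n − 2 degrees of freedom and noncentrality 7.41 / (7.53 × √(2/n)) exceeds the one-sided critical value. The noncentrality is 7.41/2.953 = 2.51 for n = 13 and 7.41/2.662 = 2.78 for n = 16.

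| Evaluable per group | one-sided 0.025 | one-sided 0.05 |
|---|---|---|
| 13 | 67% | 79% |
| 16 | 77% | 86% |

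The SD matters. With 13 per group at 0.025, an SD of 5.58 in both groups gives 90% (noncentrality 7.41/2.189 = 3.39), and 9.07 in both gives 52% (7.41/3.558 = 2.08).

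**Step 3: power to show a gain above the margin.** Replace 7.41 by 5.11. Noncentrality is 5.11/2.953 = 1.73 for n = 13, and power is 38% at one-sided 0.025.

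**Step 4: size that would carry 90% for the zero null.** The two-sample formula at one-sided 0.025 gives 2 × 10.507 × 56.70 / 7.41² = 21.7, so 22 evaluable per group.

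**The case against.** Several points on the other side stand.

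- **The mismatch alone costs no power under the printed sign.** Against the same effect, zero is an easier null than 2.3. The gap between 90% and the figures in the table comes from the missing factor 2 and the use of the smaller SD. What remains is that the 90% was computed for a different hypothesis and does not carry over.
- **The stated 13 does not prove that a margin drove the size.** A reader might infer that it can be obtained only with Δ in the formula. Two of the routes above reach it with Δ = 0. The point rests on the text, which prints Δ and defines it, and not on the arithmetic.
- **No inflated error rate follows.** If the true difference were 2.3, a zero-null t test with 13 per group and SD 7.53 would reject about 11% of the time at one-sided 0.025 and 19% at 0.05. A reader might call these false positives. For the aim as stated they are correct rejections, since the robot-assisted arm would be better, and nowhere does the protocol promise a gain above Δ.
- **Non-inferiority is not in the document.** Reading Δ that way would put power at 88% against −2.3 and 67% against zero (13 per group, 0.025). It requires reversing the printed sign and adding a factor 2, and no section mentions non-inferiority. The 21-point fall should not be charged to the plan.

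It can also be said that the analysis section names test families only and that an analysis plan, not shown here, could add a rule for Δ. That would be fair if the article were silent. It states a margin in one section and margin-free tests in the other, and offers nothing that joins them.

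**Conclusion.** The point holds as an inconsistency between the Sample size and Statistical analysis sections. The stated 90% is not the power of the comparison that will be run. For that comparison the quoted figures give about 67% to 77% at one-sided 0.025 and 79% to 86% at one-sided 0.05, for 13 to 16 evaluable patients per group.

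These figures assume normal data, a common SD of 7.53, a true difference of 7.41, and a t test in place of the repeated-measures ANOVA. They also use the SDs of the quoted scores, because no SD of the change in FMA-UE is given; a smaller SD of change would raise the power. The zero-null figures do not depend on Δ. The 38% does, and it rests on the inference that 23.00 is the control mean and that Δ is taken from it.

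The planned test itself fits the aim and need not be replaced on this account. The point should be corrected, but it leaves randomisation and data collection untouched.

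**What to change.** State one primary hypothesis and use it in both sections. The version that fits the aim is H0: between-group difference in FMA-UE change ≤ 0. Delete Δ from the Sample size section, use the two-sample formula with its factor 2, name the SD and say which group is the control, and restate the power for the planned 32 patients at the α that the Statistical analysis section will use.

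If the margin is truly intended, keep it, give its sign, its value in points and its source, and add a decision rule: compare the confidence limit of the between-group difference in FMA-UE change with Δ. The power should then be restated for that rule.

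Either version changes wording in two sections and needs no added patients or data. The cost is that the stated power falls below 90% on the quoted figures or, with a superiority margin, that the claim becomes much harder to reach.

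### For a two-arm superiority comparison, 13 per group does not give the stated 90% power on the protocol's own planning figures

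*Protocol article*

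**What the plan says.** All the planning inputs are in the Sample size section of the protocol article. The reference values are given as "The means and standard deviations (SDs) of FMA-UE scores in the two groups were 30.41 ± 9.07, 23.00 ± 5.58". The error rates are "Assuming one-sided *α* = 0.025 and one-sided *β* = 0.1". On the margin: "The value of Δ is 10% of the mean of the control group in the previous similar study". The printed formula is n = (Zα + Zβ)²σ² / (u_r − u_c − Δ)², where n "is the required number of each group". The result is "The required sample size is 13 in each group; Considering a 20% dropout rate, a total of 32 participants should be recruited", that is, 16 per arm.

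The section does not say which σ was used, whether Δ is positive or negative, or whether Δ is a superiority or a non-inferiority margin.

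The Abstract and the Discussion both ask whether the robot-assisted therapy is better than the comparator, which is a superiority question. In the Statistical analysis section, "the comparison between the two groups is used Two-way repeated measures analysis of variance", with no margin mentioned, and testing is one-sided at 0.05.

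**The concern.** For a comparison of two independent means, the per-group sample size has 2σ² (or σ₁² + σ₂²) in the numerator. The printed formula has σ² alone. If σ is the common SD, the formula halves the requirement. If σ² was meant as the sum of the two variances, the formula is sound but does not return 13. Either way, the stated 13 looks too small for the stated difference, SDs, alpha and beta.

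The stake is how the result will be read. A reader will take beta = 0.1 at face value. A non-significant result would then count as fairly strong evidence against a benefit of the assumed size, although the design would miss that benefit considerably more often than one time in ten.

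**Working it through.** **Inputs (Sample size section).** Means 30.41 and 23.00, so the difference is 7.41. SDs 9.07 and 5.58. One-sided alpha 0.025, beta 0.1.

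**Assumptions.** Equal arms for pooling: (9.07² + 5.58²)/2 = (82.26 + 31.14)/2 = 56.70, so the pooled SD is 7.53. Δ = 10% of 23.00 = 2.3; this is an assumption because the sentence on Δ cites a different reference from the one for the means, and no other control mean is given.

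**Constant.** (1.960 + 1.2816)² = 10.507.

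**Reproducing the stated 13 at the stated alpha and beta.** I tried the pooled SD, each arm's SD, their average and the root of the summed variances, with and without the factor 2, and with Δ of either sign or zero. These readings give 13:
- Two-sample variance with the pooled SD and Δ added to the difference, as in non-inferiority: 2 × 10.507 × 56.70 / (7.41 + 2.3)² = 12.64 → 13.
- Printed formula, no factor 2, smaller SD only, Δ subtracted: 10.507 × 31.14 / (7.41 − 2.3)² = 12.53 → 13.
- Smaller SD only, Δ = 0, exact t test: power is 90.1% at 13 per group.

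The first answers a non-inferiority question. The other two discard the 9.07 quoted in the same sentence. Changing alpha or beta can also produce 13: one-sided 0.05 with beta 0.2, the pooled SD and Δ = 0 gives 12.77. That contradicts the stated error rates and would be a design with 80% power.

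**Superiority sizes at the stated alpha and beta, pooled SD.**

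| Reading | Calculation | n per group |
|---|---|---|
| Printed formula, Δ = 2.3 | 10.507 × 56.70 / 5.11² = 22.8 | 23 |
| Two-sample, Δ = 0 | 2 × 10.507 × 56.70 / 7.41² = 21.7 | 22 (23 by exact t) |
| Two-sample, Δ = 2.3 | 2 × 10.507 × 56.70 / 5.11² = 45.6 | 46 (47 by exact t) |

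With the two-sample variance and the pooled SD, no Δ of zero or more can give 13, since Δ = 0 already needs 22. That conclusion does not depend on the assumed 2.3.

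**Power for 7.41 points.** Noncentral t, pooled SD, Δ = 0, noncentrality 7.41 / (7.53 × √(2/n)), which is 2.51 at n = 13 and 2.78 at n = 16:

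| Analysed per group | One-sided 0.025 | One-sided 0.05 |
|---|---|---|
| 13 | 67% | 79% |
| 16 | 77% | 86% |

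**Difference detectable with 90% power** at one-sided 0.025: about 10.0 points with 13 per group and 8.9 with 16, against the planned 7.41.

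**Sensitivity to the SD** (13 per group, one-sided 0.025, Δ = 0): 52% with SD 9.07 and 90% with SD 5.58.

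**The case against.** Four points can be made for the plan.

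First, a reader might infer that 13 cannot be obtained from the stated inputs at all. The document does not support that. With σ and Δ undefined, 13 can be reached from those inputs, and nothing shows which reading the authors used. What remains is that the readings found at the stated alpha and beta do not suit a two-arm superiority trial.

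Second, a reader might take 67% as the power of this trial. It is conditional on the pooled SD, 13 completers per group, alpha 0.025 and a plain t test on scores. The Statistical analysis section tests at 0.05, where power is higher. The primary outcome is a mean change, analysed by repeated measures, while the quoted SDs are for scores. If baseline and later scores are strongly correlated, the planned analysis could do better. This objection stands as a limit on any single figure. It does not rescue the 90% claim: the protocol gives no correlation or SD of change, and on the inputs it does give, none of the four combinations of alpha and number analysed reaches 90%.

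Third, one could quote a much lower power against the 2.3 margin. That would be power for a test that the Statistical analysis section does not describe, resting on an assumed value of Δ, so it should not be used to characterise the trial.

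Fourth, one might fault 16 per group for leaving 12.8 rather than 13 after 20% dropout. Multiplying 13 by 1.2 gives 15.6, which rounds up to 16; the discrepancy is one of rounding and not worth raising.

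**Conclusion.** The point holds in this form: the Sample size section claims 90% power with 13 per group, and for a superiority comparison on its own figures that is not so. The requirement is 22 per group with Δ = 0, or 46 with a subtracted margin of 2.3. Approximate power for 7.41 points lies between 67% (13 analysed, one-sided 0.025) and 86% (16 analysed, one-sided 0.05). At the planning alpha, the assumed benefit would be missed about one time in three with 13 analysed and about one in four with 16.

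These figures assume that the quoted SDs apply to the score compared, that they may be pooled with equal weight, and that a t test is an adequate stand-in. Power under the planned change or repeated-measures analysis cannot be computed from the document and may be higher or lower. The missing definitions of σ and Δ and the mismatch between planning alpha and analysis alpha are part of the same defect, because no power statement can be checked until they are settled.

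**What to change.** Keep 32 patients and rewrite the Sample size paragraph:

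- Put 2σ² (or σ₁² + σ₂²) in the numerator and say which σ is used.
- State the hypothesis as superiority with Δ = 0, matching the Statistical analysis section, and remove the margin.
- Use one alpha in both sections; one-sided 0.025, as planned, is the natural choice. Otherwise the restated power will still not describe the test to be run.
- Replace the 90% claim with achieved power and its assumptions. Suggested wording: With a pooled SD of 7.53 and a difference of 7.41 points, power at one-sided 0.025 is about 67% with 13 and 77% with 16 evaluable patients per group; the difference detectable with 90% power is about 10.0 and 8.9 points respectively.
- Baseline adjustment may be mentioned as a possible gain, but give no figure for it unless a correlation is stated and justified.

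The cost is one rewritten paragraph and one changed alpha in the Statistical analysis section. No patients are added. The stated power becomes less favourable, and a null result will have to be reported with that in view.

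### The printed sample-size figures do not quite fit: 16 per group less 20% dropout leaves 12.8, just under the 13 stated as required

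*Protocol article*

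**What the plan says.** The Sample size section of the protocol article bases the calculation on FMA-UE, the primary outcome. It gives the base requirement as "The required sample size is 13 in each group" and goes straight on to the recruitment target: "Considering a 20% dropout rate, a total of 32 participants should be recruited (16 per group"). It prints a formula for the base number but none for the dropout step. The Randomization and allocation section carries the total forward: "Thirty-two eligible patients are randomly divided into VRMT group and RAVRMT group in a ratio of 1:1".

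**The concern.** A dropout allowance is meant to leave the required number of evaluable patients after the assumed losses. Here the reader has all three figures (requirement, loss rate, recruitment target) and can check them against each other. At the plan's own loss rate, the target leaves slightly fewer than the plan's own requirement. The design is therefore said to have a protection that it does not quite have. What is at stake is the accuracy of one sample-size statement, and which inflation rule would be used if the base number were revised.

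**Working it through.** **Inputs, all from the Sample size section.** Requirement 13 per group; dropout 20%; recruitment 16 per group, 32 in total.

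**Forward check.** Expected evaluable per group = 16 × (1 − 0.20) = 12.8. The shortfall is 13 − 12.8 = 0.2 per group (25.6 against 26 in total).

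**Backward check.** Number needed = 13/(1 − 0.20) = 16.25, rounded up to 17 per group, 34 in total. Seventeen leaves 17 × 0.8 = 13.6.

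**Whole patients.** Sixteen keeps 13 if at most 3 are lost: 3/16 = 18.75%. A fourth loss leaves 12.

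**Can the printed 16 be reproduced?** Yes, in more than one way.

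1. Multiplying the rounded requirement: 13 × 1.2 = 15.6, rounded up to 16.
2. Dividing an unrounded requirement by 0.8. This needs the base number to be rebuilt. The stated inputs are "Assuming one-sided *α* = 0.025 and one-sided *β* = 0.1", so (1.960 + 1.282)² = 10.507, and "FMA-UE scores in the two groups were 30.41 ± 9.07, 23.00 ± 5.58", a difference of 7.41. For the margin, "The value of Δ is 10% of the mean of the control group in the previous similar study [24"]. I assume that control mean is 23.00, giving Δ = 2.30, although the margin sentence cites a different reference from the means. The article does not say which SD was used for σ. Two choices give 13:
   - The printed formula with the smaller SD: 10.507 × 5.58² / (7.41 − 2.30)² = 12.53, rounded up to 13. Then 12.53/0.8 = 15.66, rounded up to 16.
   - A two-group form (factor 2) with variance (9.07² + 5.58²)/2 = 56.70 and the margin added rather than subtracted: 2 × 10.507 × 56.70 / (7.41 + 2.30)² = 12.64, rounded up to 13. Then 12.64/0.8 = 15.80, rounded up to 16.

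**Size in power, on the two input sets that give 13 (normal approximation).**

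| Evaluable per group | First set | Second set |
|---|---|---|
| 13 | 91.0% | 90.8% |
| 12.8 | 90.6% | 90.4% |
| 12 | 88.7% | 88.5% |

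Going from 13 to the expected 12.8 costs about 0.4 of a percentage point, and the nominal 90% is kept.

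**The case against.** The strongest reply is that rounding once, at the end, is legitimate. If the authors carried 12.53 or 12.64 through a correct division by 0.8, they would reach 16 without error, and 12.8 expected completers would exceed that unrounded need. This stands as far as the cause is concerned. A reader might infer that the allowance was applied by multiplying by 1.2, because 13 × 1.2 rounds up to 16. The article does not support that as fact: it gives no inflation formula, and both routes end at 16. For the same reason it cannot be said that a revised base number would necessarily come out too small at this step.

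The reply does not remove the mismatch. The article states its requirement as 13, and that is the figure a reader can hold it to. The unrounded values are reconstructions: one uses only the smaller SD in a formula without the two-group factor of 2, and the other reverses the sign of the margin against the printed formula. In whole patients, a fourth loss leaves 12, which is below 12.53 and 12.64 as well as 13.

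It is also fair to say that the quantity is trivial and that 20% is a round planning figure. That is right, and it sets the severity.

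**Conclusion.** The point holds as a minor inconsistency. On the figures as printed, 16 per group does not absorb 20% dropout and keep 13. It absorbs up to 18.75%. The gap is 0.2 of an expected patient per group, or one patient per group in the target (16 against 17; 32 against 34 in total).

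A reader might infer a material loss of power from this step. The documents do not support that: on either set of inputs that yields 13, power at 12.8 stays above 90%. Those power figures depend on the assumed Δ of 2.30 and on the reconstructed choice of σ and formula. The comparison of 12.8 with 13 depends on neither.

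The finding takes 13 as given. Whether 13 is itself well founded is a separate question about the Sample size section, and any power loss from that source should not be counted here.

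**What to change.** Change one sentence in the Sample size section, in one of two ways:

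- Keep 32 patients and state that 16 per group leaves 13 evaluable per group provided dropout does not exceed 18.75% (3 of 16). This needs no extra patients. The only cost is a slightly less favourable stated allowance.
- Keep the 20% rate and state 17 per group, 34 in total. This costs two more patients, and the total in the Abstract and in Randomization and allocation must change to match.

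In either case, state the rule used, n/(1 − dropout), and whether it is applied to the rounded or unrounded n. Use the same rule if the base number is revised. The choice of rule matters a little more at larger n: a base of 22 would give 22/0.8 = 27.5, so 28, against 22 × 1.2 = 26.4, so 27; a base of 46 would give 57.5, so 58, against 55.2, so 56.
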